## Abstract

**Background:**

The school system has been identified as an ideal setting for the implementation of prevention and early intervention programs for suicide. However, in Australia, suicide-prevention programs that are routinely delivered in the schools are lacking. Internationally, evidence exists for the effectiveness of peer-led interventions that take a social connectedness approach to improve help-seeking for suicide. The aim of the current trial is to test the effectiveness of the Sources of Strength program to promote help-seeking for suicide in adolescents in Australian high schools.

**Methods/design:**

This study is a two-arm, cluster-randomised, controlled trial that will compare the evidence-based Sources of Strength program to a wait-list control condition. Sixteen Australian high schools will be recruited to the trial, with all adolescents in years 7 to 10 (12–16 years of age) invited to participate. Peer leaders from intervention-condition schools will receive training in the Sources of Strength program and will integrate positive messages, across 3 months, with the support of adult advisors. Activities may take the form of class presentations, posters, videos, and messages on social media sites and will aim to change help-seeking norms, strengthen youth-adult connections, and promote positive coping. The primary outcome measure for the study is help-seeking intentions, whereas secondary outcomes include help-seeking behaviour, help-seeking attitudes and norms, referral of distressed peers, availability of adult help, positive coping, and suicidal behaviour. Data will be collected pre-intervention, post-intervention (after the initial 3 months of messaging), and at the end of the first (6-month follow-up) and the second year after implementation (18-month follow-up). Primary analyses will compare changes in help-seeking intentions for the intervention condition relative to the wait-list control condition using mixed-effect repeated-measures analyses to account for clustering within schools.

**Discussion:**

If proven effective, this universal social connectedness program for suicide could be more widely delivered in Australian high schools, providing a valuable new resource. The Sources of Strength program has the potential to significantly contribute to the mental health of young people in Australia by improving help-seeking for suicide. The findings from this research will also contribute to the evidence-base for peer-leadership programs internationally.

**Trial registration:**

Australian New Zealand Clinical Trials Registry, ACTRN12616000048482. Registered on 19 January 2016.

**Electronic supplementary material:**

The online version of this article (doi:10.1186/s13063-016-1475-1) contains supplementary material, which is available to authorized users.

## Background

Youth suicide is a significant public health problem. In 2013, suicide was the leading cause of death in young Australians aged 15–24 years. For Australian males aged 15–19 years, the annual suicide rate was 14.3 per 100,000 people and accounted for 34.8 % of total deaths, whereas for Australian females, the suicide rate was 5.6 per 100,000 people and accounted for 26.1 % of total deaths [1]. This equates to more than 12 suicides per month across Australia in this age group. Suicidal ideation and attempts among young people are also a significant concern. In a systematic review of suicide phenomena in young people worldwide, the mean proportion of adolescents reporting a lifetime suicide attempt or suicidal thoughts was 9.7 % and 29.9 %, respectively [2].

The significant burden associated with suicide is evident from the fiscal and societal costs associated with youth suicidal behaviour (ideation, attempts, and suicide deaths) such as emotional and psychosocial morbidity, medical care, lost productivity, and the secondary distress caused to family members and friends [3]. In 2003, suicide accounted for 21 % of total years of life lost for Australians aged 15–24 years and 7.1 % of disability adjusted life years for males of the same age. Non-fatal suicidal behaviour was also related to substantial disability and loss of years of healthy life [4].

The prevalence of youth suicide, and the significant burden associated with it, has given rise to the development of a range of interventions aimed at the prevention of suicidal behaviour and the promotion of help-seeking and early identification for suicide. The need to promote and assist help-seeking behaviour among youth is critical, as young people often do not seek or receive help for suicidal thoughts and behaviour [5–8]. Interventions for youth suicide prevention have been implemented in schools, communities and healthcare systems and are designed to reduce risk factors for suicidal behaviour or to identify individuals at risk and provide pathways to treatment or support [5, 9]. Schools have been identified as an ideal setting for the implementation of these interventions, as they provide a cost-effective and convenient way of reaching young people who spend a significant period of their time there, and schools are a key social setting for identifying problems and offering support [7, 10]. Depending on the approach employed, these programs can be delivered universally, to all students or staff in a school or classroom setting, or to a selective (at-risk) or indicated (early signs) group of students or staff [9].

Reviews of school-based suicide prevention interventions [5, 9, 11, 12] conclude that the evidence-base for existing programs is limited, with the need for more rigorous evaluations, randomised controlled trials and the inclusion, where feasible, of suicidal behaviour outcomes. One of the promising suicide prevention programs identified in the reviews of school-based programs [9] is the universal Sources of Strength peer leadership program [10, 13], which takes a social connectedness approach to improving help-seeking for suicide and general psychological distress. Social isolation and thwarted belongingness have been identified as risk factors for suicide [14]. The Sources of Strength program is designed to build socioecological protective influences across an entire school student population and focuses on enhancing help-seeking norms, youth-adult communication, and coping skills to promote help-seeking [10, 13].

With the support of adult mentors, peer leaders from diverse social groups are trained to conduct whole-school messaging activities that are intended to change peer-group norms, attitudes and behaviours. The program harnesses the social networks of the peer leaders to disperse the program’s messages. More specifically, the peer leaders are taught to model and encourage friends to (a) reinforce and create an expectancy that friends ask adults for help for suicidal friends, thereby increasing the acceptability of seeking help and reducing implicit suicide acceptability; (b) name and engage ‘trusted adults’ to improve communication and connections between youth and adults; and (c) identify and use interpersonal (e.g. family and positive friends) and formal coping resources (e.g. mental health services and positive activities) to promote healthy coping attitudes. An integral part of the program is the identification and utilisation of eight key protective factors, referred to as ‘sources of strength’. These sources encompass family support, positive friends, caring adults, positive activities, generosity, spirituality, mental health access, and medical access. Overall, the program acts to reduce suicidal behaviours by more effectively connecting suicidal youth with capable adults and prevent the development of suicidal behaviour by promoting positive coping for psychological distress (e.g. depression and anxiety) [10, 13].

The Sources of Strength program has been evaluated in a randomised controlled trial of 18 high schools, 453 peer leaders, and 2,675 students located in the USA [10]. Peer leaders in intervention schools undertook whole-school messaging over a 3-month period, with pre- and post-messaging questionnaires conducted. Consistent evidence was found for a positive intervention effect on the norms, attitudes, and behaviour of both peer leaders and the wider student population. In particular, training improved the peer leaders’ adaptive norms regarding suicide (Cohen’s *d* effect size = 0.34–0.75), their connectedness to adults (*d* = 0.49–0.62), and their school engagement (*d* = 0.22). Peer leaders also reported increased support to peers (*d* = 0.34) and a greater connection of distressed peers to adults (*d* = 0.21), with peer leaders referring suicidal friends to an adult four times more than untrained peer leaders in control schools. Among the wider student population, the program increased perceptions of adult support for suicidal youth (*d* = 0.63) and the acceptability of seeking help (*d* = 0.58). The perception of adult support increased the most in students with a history of suicidal ideation. The fidelity of the intervention was also assessed through school-based staff interviews, finding that 97.2 % of staff had observed or received intervention-specific messages, and 88.9 % of those named as ‘trusted adults’ had been contacted by a peer leader as the intervention had intended. Overall, the changes observed in the intervention schools were congruent with the immediate goals of the Sources of Strength program, which were to enhance norms pertaining to suicide help-seeking, increase knowledge of capable adults, and increase acceptability of engaging adults for help within student peer groups.

The program promotes help-seeking for suicide by changing norms about help-seeking for suicide, which traditionally has seen young people not seeking help from adults due to negative beliefs about professional help, ‘codes of silence’ (shame and self-stigma, fears about disclosure, and a lack of trust that others will understand) and attitudes promoting self-reliance [6, 7]. Peer leaders recruited to the program work to change these norms by promoting and modelling help-seeking behaviour and positive communication with ‘trusted adults’, as well as the utilisation of multiple sources of strength in times of distress, discouraging self-reliance. These actions work to normalise help-seeking behaviour and increase its acceptability [3, 8].

The project represents the first evaluation of the Sources of Strength program within the Interpersonal Theory of Suicidal Behavior. This theory posits that three key interpersonal constructs are central to suicidal behaviour: thwarted belongingness, perceived burdensomeness, and acquired capability for suicide [15]. The combination of thwarted belongingness and perceived burdensomeness is strongly associated with the development of suicidal desire, whereas serious suicidal behaviour only occurs when acquired capability for suicide is also present [14–16]. The Sources of Strength program has been postulated to act to reduce thwarted belongingness through its promotion of youth-adult connections and that the utilisation of Sources of Strength will promote positive coping, effectively reducing social isolation and encouraging reciprocally caring relationships.

### Aims of the trial

#### Primary aim

The primary aim of the trial is to test the effectiveness of the Sources of Strength intervention for increasing help-seeking intentions for suicide at post-intervention.

#### Secondary aims

The secondary aims are as follows:To test the effectiveness of the Sources of Strength intervention for increasing help-seeking intentions for suicide at 6-month follow-upTo test the effectiveness of the Sources of Strength program for (a) increasing actual help-seeking behaviour and the usefulness of adult help, (b) improving attitudes and norms towards adult help, (c) greater referral of suicidal peers, and (d) increased availability of adult help, at post-intervention and 6-month follow-upTo test the effectiveness of the Sources of Strength program for increasing positive coping (mental wellbeing, Sources of Strength (SoS) coping, social support, and mastery) at post-intervention and 6-month follow-upTo test the effectiveness of the Sources of Strength program for reducing suicidal thoughts and behaviours (plans and attempts) at post-intervention and 6-month follow-upTo test the impact of the Sources of Strength program on thwarted belongingness at post-intervention and 6-month follow-upTo test if the Sources of Strength intervention effects are increased at 18 months following the second year of program implementation

#### Subsidiary aims

Subsidiary aims include the following:Levels of student and staff exposure to Sources of Strength whole-school messaging will also be explored, including a *social network* analysis in a subset of intervention schools to determine whether peer leader messaging increases the density of positive social ties across students and increases positive connections to adults, particularly among isolated students. The social network investigation will also test engagement with social media messages posted by peer leaders at the intervention schools, accounting for both virtual and self-reported social networks within each school.Data collected from the study will also be used to test models of *suicide risk*, including the Interpersonal Theory of Suicidal Behavior [14, 15] and the relationship between positive future thinking and suicide risk [17]. These models will explore a range of potential risk and protective factors, such as perceived burdensomeness, thwarted belongingness, acquired capability for suicide, entrapment, self-harm, depressive and anxiety symptoms, personality, and risk-taking. Analyses will be conducted cross-sectionally and prospectively.Lastly, *predictors and mediators* of intervention effects and intervention engagement will also be explored, including demographic characteristics, suicide stigma, suicide literacy, suicidal ideation, depressive symptoms, bullying, school inclusion, risk taking and personality profiles, peer leader status and exposure to messaging. These analyses will also investigate subgroup effects, such as whether there are greater effects on help seeking intentions and coping among students with suicidal ideation compared to those without.

#### Trial hypotheses

At post-intervention and 6-month follow-up, participants in those schools receiving the Sources of Strength program, relative to participants in the wait-list control schools, will have:Increased help-seeking intentions for suicide(a) Increased actual help-seeking behaviour for suicide, more positive attitudes and norms associated with adult help for suicide, increased referral of suicidal peers, and greater perceived availability of adult help for suicidal peers(b) Increased positive coping, which is demonstrated by higher mental wellbeing, greater endorsement of SoS coping, more positive social support and higher mastery(c) Lower levels of suicidal ideation, plans, and attempts(d) Decreased levels of thwarted belongingness, thus reducing suicide susceptibility

Furthermore:2.(e) Within-school effects at intervention schools will be stronger at 18 months (as the messaging program matures) than at 6 months.

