## Methods/design

### Study design

This study will be implemented as a two-arm, cluster-randomised controlled trial (RCT), with an intervention condition (Sources of Strength program) and 24-month wait-list control condition. Measurements will be taken on four occasions: pre-intervention, post-intervention (after 3 months of messaging), and in two follow-ups at the end of each school year (approximately 6- and 18-month follow-up). This study was granted ethical approval by the Australian National University Human Research Ethics Committee (protocol number 2015/199) and the individual State and Territory education departments (Catholic Education Office Archdiocese of Canberra & Goulburn, ACT Government Education and Training Directorate, and the NSW Government Department of Education) responsible for schools in the recruitment districts.

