At the completion of the messaging phase, the post-intervention questionnaire will be administered to all students. A short survey will also be administered to all staff in intervention condition schools to assess the reach of the whole-school messaging and youth-adult connections. A 6-month follow-up questionnaire will also be administered to all students towards the end of the first year of the program.

In the second year of the project, a refresher Sources of Strength peer leadership training will be provided, with new adult advisors and peer leaders invited to participate alongside previous participants. This will be followed by a second 3-month whole-school messaging phase. A final 18-month follow-up questionnaire will be conducted at the end of the second year. After the completion of all questionnaires, schools in the wait-list control condition will be offered the Sources of Strength program, including the training of adult advisors and peer leaders, but questionnaires will not be administered. Figure 1 presents the flow of participants in the trial (See Additional file 1: Attachment A for SPIRIT Checklist).

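### Hypothesis 2(e) words the 18-month question as a within-school comparison in intervention schools only, so an analysis that follows it could mistake ageing or calendar time for a maturing program effect

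*Protocol article*

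**What the plan says.** Under Trial hypotheses, hypotheses 1 and 2(a) to 2(d) share one stem: at post-intervention and 6 months, participants in program schools, "relative to participants in the wait-list control schools, will have" the listed outcomes. The list then leaves that stem and adds 2(e): "Within-school effects at intervention schools will be stronger at 18 months (as the messaging program matures) than at 6 months". No comparator is named.

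The matching item under Secondary aims is to test whether "intervention effects are increased at 18 months following the second year of program implementation".

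On the availability of controls:
- Study design sets a "24-month wait-list control condition" and schedules four measurement occasions, the last two at about 6 and 18 months, with no restriction to one arm.
- Procedure states: "A final 18-month follow-up questionnaire will be conducted at the end of the second year". It then adds: "After the completion of all questionnaires, schools in the wait-list control condition will be offered the Sources of Strength program".
- In Table 1 (Assessments), only the reach and fidelity items are footnoted as confined to intervention schools.

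Statistical analysis describes school-clustered mixed models on all randomised participants. It spells out one between-arm contrast for help-seeking intentions, from pre- to post-intervention. The one analysis it names at 18 months is the difference in relative risk of suicide attempt from baseline to the 6- and 18-month follow-ups.

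**The concern.** An intervention effect in a two-arm randomised trial is a difference between arms, and the secondary aim is phrased in those terms. Hypothesis 2(e) instead describes change over time inside treated schools and attributes it to the program maturing.

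The participants are adolescents (the abstract has "all adolescents in years 7 to 10 (12–16 years of age) invited to participate"), and they are a year older at 18 months than at 6 months. Help-seeking, coping and suicidality may shift with age, with calendar time, or because the same questionnaire has been completed several times. In a single-arm comparison such shifts cannot be separated from any gain from the second program year. They can act in either direction: an upward drift could look like growth in effect, and a downward drift could hide real growth. At stake is the claim that a second year of messaging adds benefit.

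**Working it through.** **1. Wording set side by side.**

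| Place | Comparison | Occasions |
|---|---|---|
| Hypotheses 1, 2(a)–(d) | Program schools against wait-list schools | Post-intervention, 6 months |
| Hypothesis 2(e) | Within intervention schools | 18 against 6 months |
| Last secondary aim | Intervention effects increased; comparator not named | 18 months |
| Statistical analysis, primary contrast | Change in one arm against change in the other | Pre to post |
| Statistical analysis, suicide attempts | Difference in relative risk | Baseline to 6 and to 18 months |

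Randomisation allocates each school to a single condition, so a within-school effect in an intervention school can only be change over time. No row gives a controlled 18- versus 6-month contrast.

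**2. The plan's own figures.** The article gives no number for 2(e). Its sample size reproduces closely. For d = 0.33, variance of change 2(1 − 0.5) = 1, two-sided 5% and 80% power, n = 145 per arm. The design effect is 1 + 299 × 0.04 = 12.96, and 145 × 12.96 = 1,879.2. Dividing by 0.8 gives 2,349 per arm, against the stated 2,400 (8 × 300). Nothing in this point changes that figure.

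**3. Expectation of the two contrasts.** Let D be drift from 6 to 18 months shared by all schools, and G the true growth in program effect.
- Within-arm contrast: D + G.
- Two-arm contrast: (D + G) − D = G.

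With G = 0, the within-arm contrast estimates D.

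**4. Illustration of size.** Inputs and sources:
- 8 intervention schools: Sample size and power calculations.
- 240 completers per school = 300 × 0.8. The 300 and the 20% are stated for the post-intervention calculation; carrying them to 18 months is an assumption.
- Correlation of 0.5 between 6 and 18 months, so variance of change is 1. This is an assumption; the article gives 0.5 for baseline to endpoint.
- ICC of change 0.04, 0.016 or 0.01. This is an assumption; the article's 0.04 and 0.02 are not ICCs of 6-to-18-month change.
- Drift 0.02, 0.05 or 0.10 SD. This is an assumption; the article gives no age trend.

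Standard error within arm = √[(1 + 239 × ICC) / 1,920], since 8 × 240 = 1,920. Rejection rate from the non-central t with 7 df, non-centrality = drift / SE, critical value 2.365, G = 0:

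| ICC of change | SE within arm | Drift 0.02 | Drift 0.05 | Drift 0.10 |
|---|---|---|---|---|
| 0.04 | √(10.56/1,920) = 0.074 | 6% | 9% | 22% |
| 0.016 | √(4.824/1,920) = 0.050 | 6% | 14% | 41% |
| 0.01 | √(3.39/1,920) = 0.042 | 7% | 18% | 54% |

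The two-arm contrast has SE √2 ≈ 1.4 times larger: 0.105, 0.071 and 0.059. Its rejection rate stays at 5% provided the drift is common to both arms.

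**The case against.** A reader might infer that the trial has committed to a single-arm test and will discard the randomised comparison at 18 months. The article does not support that. A hypothesis is not an analysis, and Statistical analysis prescribes no single-arm test for any outcome. Its mixed models cover all randomised participants, and the relative-risk comparison for suicide attempts is most naturally read as an arm comparison that reaches 18 months. The word effects in 2(e) might also be meant in the controlled sense, as in the secondary aim. The 18-month work is described as subsidiary, and its exact contrast may be set out in a full protocol or analysis plan that is not shown.

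This limits the consequence to a conditional one. It does not rescue the wording. If a between-arm effect was meant, then within-school and at intervention schools are the wrong words. The relative-risk analysis covers suicide attempts only and is set against baseline, so it does not contrast 18 with 6 months. The correction concerns a framing that the article states, not a detail left for later.

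The objection to the numbers also stands in part: drift, ICC of change, the 6-to-18-month correlation and the number of completers are all assumed. At 0.02 SD drift the error rate is close to nominal.

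**Conclusion.** The point holds as a defect of wording with a conditional consequence. Hypothesis 2(e) departs from every other hypothesis and from the aim it serves. If the analysis follows it as written, ageing, calendar time or repeated testing could be attributed to program maturation, or real growth could be missed. The design supplies what is needed to avoid this: control schools remain untreated beyond the 18-month visit and are scheduled for the same questionnaires. Procedure does not repeat that all students complete the last one, but nothing restricts it to one arm.

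The range of 6–7%, 9–18% and 22–54% shows direction and sensitivity under the assumptions listed. It should not be read as an error rate measured for this trial. The 5% for the two-arm contrast depends on drift being the same in both arms.

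The primary aim, the sample size and the primary report (post-intervention and 6 months) are untouched. The change should be made, but it is not critical to the main result.

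**What to change.** Restate 2(e) as: the intervention-minus-control difference at 18 months is larger than that at 6 months, in the favourable direction for each outcome. Test it by the condition-by-occasion contrast, (18 minus 6 months in intervention schools) minus (18 minus 6 months in control schools), in the school-clustered mixed model already planned, with the binary counterpart for dichotomous outcomes. Present within-school trajectories as description and label them uncontrolled.

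The cost is one sentence and one contrast on data already scheduled. The downside is precision: the standard error is about 1.4 times that of the within-arm test, so modest growth will be harder to show.
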